## Abstract

**Background:**

A number of investigative strategies exist for the diagnosis of coronary heart disease (CHD). Despite the widespread availability of noninvasive imaging, invasive angiography is commonly used early in the diagnostic pathway. Consequently, approximately 60% of angiograms reveal no evidence of obstructive coronary disease. Reducing unnecessary angiography has potential financial savings and avoids exposing the patient to unnecessary risk. There are no large-scale comparative effectiveness trials of the different diagnostic strategies recommended in international guidelines and none that have evaluated the safety and efficacy of cardiovascular magnetic resonance.

**Trial Design:**

CE-MARC 2 is a prospective, multicenter, 3-arm parallel group, randomized controlled trial of patients with suspected CHD (pretest likelihood 10%-90%) requiring further investigation. A total of 1,200 patients will be randomized on a 2:2:1 basis to receive 3.0-T cardiovascular magnetic resonance–guided care, single-photon emission computed tomography–guided care (according to American College of Cardiology/American Heart Association appropriate-use criteria), or National Institute for Health and Care Excellence guidelines–based management. The primary (efficacy) end point is the occurrence of unnecessary angiography as defined by a normal (>0.8) invasive fractional flow reserve. Safety of each strategy will be assessed by 3-year major adverse cardiovascular event rates. Cost-effectiveness and health-related quality-of-life measures will be performed.

**Conclusions:**

The CE-MARC 2 trial will provide comparative efficacy and safety evidence for 3 different strategies of investigating patients with suspected CHD, with the intension of reducing unnecessary invasive angiography rates. Evaluation of these management strategies has the potential to improve patient care, health-related quality of life, and the cost-effectiveness of CHD investigation.

## Background

Coronary heart disease (CHD) is a leading cause of death and disability worldwide. In a typical hospital setting, a variety of investigations may be used to diagnose CHD, risk-stratify, and determine the need for coronary revascularization. Myocardial perfusion scintigraphy by single-photon emission computed tomography (SPECT) is the most commonly used test worldwide for the assessment of myocardial ischemia, and there is a large body of evidence to support its prognostic value. Cardiovascular magnetic resonance (CMR) has high diagnostic accuracy for the detection of CHD, and the CE-MARC study demonstrated CMR's superiority over SPECT.^1^ Despite the widespread availability and recommendation of noninvasive imaging investigations in national and international guidelines,^2–4^ invasive coronary angiography is commonly used early in the diagnostic pathway. Evidence from large populations of patients presenting with chest pain has confirmed that the majority will not have significant obstructive coronary disease.^5,6^ In the United States, the American College of Cardiology National Cardiovascular Data Registry identified almost 400,000 patients without known CHD that underwent elective catheterization from January 2004 through April 2008, and only 38% had obstructive CHD.^6^

Avoiding unnecessary angiography has potential financial savings and avoids exposing the patient to unnecessary risk. Invasive coronary angiography has a risk of major complications of 1.7%. Furthermore, the dose and stochastic effects of x-ray radiation are frequently misjudged,^7^ with the risk of developing a solid tumor estimated at 1:2500 diagnostic coronary angiographic procedures.^8^ Paradoxically, the implementation of UK national guidelines for the assessment and diagnosis of recent onset chest pain has been demonstrated to increase invasive coronary angiography rates between 20% and 28%.^9^

A previous single-center trial (CECaT) indicated that invasive angiography could be avoided in 20% to 25% of patients using functional testing as an initial gatekeeper.^10^ To date, there are no large-scale comparative effectiveness trials of the different diagnostic strategies recommended in international guidelines and none that have evaluated the safety and efficacy of CMR.

## Study objectives

The primary objectives are to determine if 3.0-T CMR-guided management is superior to (*a*) National Institute for Health and Care Excellence (NICE) guidelines–based management (CG95),^3^ and (*b*) SPECT-guided management,^11^ in terms of reducing the rates of unnecessary invasive angiography occurring within 12 months in patients with a pretest likelihood (PTL) of CHD of 10% to 90%.

Secondary objectives will determine (*a*) if in patients with a high PTL of CHD (61%-90%), noninvasive imaging (CMR or SPECT) is superior to NICE guidelines–based management, in terms of reducing the occurrence of unnecessary invasive angiography; (*b*) safety in terms of major adverse cardiovascular events (MACE) at 3 years between the CMR-guided care group and those receiving NICE guidelines–based management; (*c*) safety in terms of MACE at 3 years between the CMR-guided care group and those receiving SPECT-guided management; and (*d*) cost-effectiveness and impact on health-related quality-of-life (HRQoL) measures of a CMR-guided care strategy compared with NICE guidelines–based management and SPECT-guided management.

## Methods

### Study design

CE-MARC 2 (clinicaltrials.gov: NCT01664858) is a prospective, multicenter, multivendor, 3-arm parallel group, randomized controlled trial of patients referred to cardiology care for further evaluation of symptoms thought to be angina pectoris. A total of 1,200 patients with suspected CHD will be randomized on a 2:2:1 basis to receive CMR-guided care, SPECT-guided care, or NICE guidelines–based management (Figures 1 and 2).

Statistical analysis will be performed by the Clinical Trials Research Unit, University of Leeds, and the Centre for Health Economics, University of York. The study population will be followed up prospectively for a minimum of 3 years to establish long-term MACE in each investigation arm. The study will be conducted in accordance with the Declaration of Helsinki and has been approved by the National Research Ethics Service.

### Patient Population, Recruitment, and Randomization

Subjects will be considered for inclusion if they are 30 years or older presenting to participating hospitals (Appendix A) with suspected cardiac chest pain (angina) with a defined CHD PTL of 10% to 90%.^3^ Full inclusion and exclusion criteria are listed in Table I. An anonymized log of all patients screened for eligibility who are not recruited either because they are ineligible or because they declined to participate will be kept.

The treating clinician makes a clinical diagnosis of typical angina if the patient has all 3 salient features of angina (constricting discomfort in the front of the chest, or in the neck, shoulders, jaw, or arms; precipitated by physical exertion; and relieved by rest or glyceryl trinitrate within ~5 minutes) or atypical angina if they have 2 of 3.^3,12^ Those with one or none of the features are defined as nonanginal chest pain^3,12^ and ineligible for the study. The patients' risk factors (age, gender, ethnicity, abdominal and hip circumference, lipid profile, blood pressure, smoking, and diabetic status), medical history (including rheumatoid arthritis, hypertension, hyperlipidemia, peripheral vascular disease, and cerebrovascular disease), and family history of premature CHD will be recorded.

Patients will undergo risk stratification with their PTL of having CHD calculated^3,13^ and categorized as low (10%-29%), intermediate (30%-60%), or high (61%-90%). Randomization will be achieved using minimization, incorporating a random element through a computer-generated program accessed via a 24-hour telephone service. This will allocate patients in a 2:2:1 ratio between CMR/SPECT/NICE after taking account of the following stratification factors: randomizing site, age (30-64 years, ≥65 years), PTL (10%-29%, 30%-60%, 61%-90%), and gender. Those with low PTL of underlying CHD (10%-29%) randomized to NICE guidelines will undergo cardiac computed tomography (CCT), intermediate PTL (30%-60%) SPECT, and high PTL (61%-90%) coronary angiography.

### Investigation Details

#### Cardiovascular magnetic resonance

Cardiovascular magnetic resonance will be performed on a clinical 3.0-T scanner using protocols that conform to international standards.^14^ A cardiac imaging receiver coil configuration will be used, and electrocardiogram (ECG) gating will be performed. The scan will comprise the following:1.Survey and reference scans prior to defining the short, vertical long, and horizontal long axes acquired with a balanced steady-state free precession (bSSFP), single-slice breath-hold sequence. bSSFP pulse sequence parameters dependent on scanner manufacturer and site. Typical parameters are as follows: echo time 1.3 milliseconds, repetition time 2.6 milliseconds, flip angle 40°, field of view 320-420 mm according to patient size, SENSE or GRAPPA acceleration, slice thickness 10 mm, and 30 phases per cardiac cycle.2.Stress perfusion imaging performed with adenosine administered initially at 140 μg kg^−1^ min^−1^. Adequate hemodynamic response is assessed by either ≥10% heart rate increase or ≥10 mm Hg decrease in systolic blood pressure. If there is inadequate hemodynamic response, then the dose will be increased incrementally to 170 μg kg^−1^ min^−1^ and then 210 μg kg^−1^ min^−1^ for a further 2 minutes until hemodynamic response is achieved.Perfusion image acquisition will use a 2-dimensional, *T*_1_-weighted saturation recovery–prepared gradient echo-pulse sequence in 3 short-axis slices, planned using the 3/5 technique,^15^ using either parallel imaging acceleration (SENSE or GRAPPA) or spatiotemporal undersampling (5× *kt*-BLAST). First-pass contrast-enhanced study will be performed using a dual-bolus technique (0.075 mmol/kg gadobutrol [Gadovist; Bayer Schering Pharma, Berlin, Germany]) for the main bolus preceded by the same volume of a 10% dilute contrast agent dose for the prebolus, both administered at a rate of 4.0 mL/s followed by a 20-mL saline flush.3.Resting wall motion and left ventricular function will be assessed with a contiguous stack of multiphase ventricular short-axis bSSFP cines (10-12 slices, 30 phases, 10-mm slice thickness, 0-mm gap, same cine pulse sequence as above).4.The rest myocardial perfusion study will use identical pulse sequence, slice positioning, and injection characteristics to the stress perfusion scan. If the stress perfusion scan was not of adequate quality (eg, ectopics and failure to trigger), a repeat stress may be performed as alternative to the rest study.5.Late gadolinium enhancement (LGE) performed in 10 to 12 short-axis slices 10 to 15 minutes after step 4 with an inversion recovery–prepared *T*_1_-weighted gradient echo-pulse sequence. Typical parameters are as follows: echo time 2.0 milliseconds, repetition time 3.7 milliseconds, flip angle 25°, acquired spatial resolution 0.70 × 0.70 × 10 mm^3^, and inversion time individually adjusted according to inversion time scout. LGE will be acquired with alternate heart beat acquisition (with single-shot or navigated LGE, an option for poor breath holders) and long-axis and modified views acquired if clinically indicated.

#### Single-photon emission computed tomography

Radionuclide imaging will be performed according to local standard departmental practice conforming to both national and international guidelines.^16–18^ Patients will undergo either a 1- or 2-day scanning protocol with a radioisotope tracer ^99m^Tc-tetrofosmin or ^99m^Tc-sestamibi (Myoview, GE Healthcare and CARDIOLITE, Lantheus Medical Imaging). A weight-adjusted dose up to a maximum of 1000 MBq per examination will be used for stress and rest imaging, which will be performed within 5 days of each other.

Stress examination will be performed with either treadmill or bicycle exercise, pharmacologic vasodilator stress (with adenosine or regadenoson), or a combination. Treadmill will involve exercise using the BRUCE or modified BRUCE protocol or bicycle ergometer typically commencing at 25 W increasing workload by 25 W every 2 minutes. Radioisotope tracer will be injected at peak stress.

If pharmacologic stress with adenosine is used, the administration regimen will be comparable with the CMR protocol. If regadenoson is used, 0.4 mg will be delivered by rapid intravenous injection. Radioisotope tracer will be injected after at least 4 minutes of adequate hemodynamic/symptom response. Vasodilator stress may be combined with submaximal exercise.

Images will be acquired on either a dual headed gamma camera or solid-state cadmium zinc telluride camera. Stress and rest images will be gated to the ECG, and attenuation correction will be used where routinely available.

#### Cardiac CT

Cardiac computed tomography will be performed on a minimum 64-slice multidetector CT and follow international guidelines.^19^ Coronary artery calcium (CAC) scoring scan protocol will involve the following:1.Scout scans.2.Unenhanced scan with prospective gating and inspiratory breath-hold. A minimum scan length (*z*-axis distance) will be used from tracheal bifurcation to the inferior border of the heart.3.Agatson CAC score will be calculated and NICE guidance followed.^3^ If CAC is 0, no further imaging will be performed; if CAC score is 1 to 400, proceed to CT coronary angiography (CTCA); and if CAC score is >400, refer for invasive coronary angiography.

For CT coronary angiography, heart rate control will be achieved with β-blockade (intravenous or oral) and short-acting sublingual nitrates given. Computed tomography coronary angiography will be performed where possible, with a prospective gating technique using the minimum scan range planned from the unenhanced scan. Typical scan parameters are as follows: 0.625-mm collimation, pitch 0.2-0.4, 100-120 kV, and 400-830 mAs (adjusted according to body mass index). If retrospective gating is required, ECG dose modulation will be used to minimize radiation dose. The acquisition window will usually be centered at end-diastole (end-systole may be used at the discretion of the attending physician). In those with variable heart rates, time interval padding may be used to allow reconstruction of both the systolic and diastolic phase data sets. The exact scan parameters and radiation reduction algorithms used will be dependent on the hardware vendor. Iodinated contrast agent of 60 to 120 mL will be administered at a flow rate of 4.5 to 6.5 mL/s, followed by a bolus of normal saline (eg, 50 mL and 5 mL/s) during an acquisition with inspiratory breath-hold. Either a test bolus or a bolus tracking technique may be used.

#### Invasive angiography and Fractional Flow Reserve

Angiography will be performed using a standard technique (radial or femoral approach). Fractional flow reserve (FFR) (PressureWire; St Jude Medical, Minneapolis, MN) will be performed in all vessels ≥2.5 mm with stenosis ≥40% and ≤90%, following intracoronary nitrates, using adenosine at 140 to 210 μg kg^−1^ min^−1^ to achieve maximal hyperemia and hemodynamic steady state; pull-back assessment of diffuse disease or serial stenoses can be made. Adenosine will be administered as per CMR protocol. Totally occluded coronary arteries will have a default FFR value of 0.50 recorded; for lesions >90%, FFR will also be considered positive (0.50), and for lesions <40%, FFR will be considered normal (0.90).^20^ All sites will have FFR quality assurance core laboratory assessment of the FFR recordings using vendor software (RADIVIEW 2.2; St Jude Medical Corp).

### Investigation reporting

All test results will be reported by independent cardiology/radiology consultants with a minimum 5-year experience in the imaging modality. In accordance with usual clinical practice, all clinical data from all noninvasive imaging modalities will be available for the reporting physician to make an overall clinical judgement.

#### Cardiovascular magnetic resonance

Cardiovascular magnetic resonance analysis will be both visual and quantitative following international recommendations.^21^ Local on-site reporting will include regional wall motion abnormalities (by visual analysis using the 17-segment American Heart Association/American College of Cardiology model). Each segment scored as 0 = normal, 1 = mild hypokinesia, 2 = severe hypokinesia, 3 = akinesia, or 4 = dyskinesia. Quantitative analysis will include the following: end-diastolic volume (mL), end-systolic volume (mL), stroke volume (mL), and ejection fraction (%).

Detection of hypoperfusion (ischemia), by visual comparison of stress, rest, and LGE scans, will be scored as 0 = normal, 1 = equivocal, 2 = nontransmural ischemia <50%, 3 = nontransmural ischemia ≥50%, or 4 = transmural ischemia in 16 segments of the 17-segment American Heart Association/American College of Cardiology model (excluding the apical cap).

Any infarct (scar) will be reported based on the LGE images (17-segment model), with scores of 0 = no hyperenhancement, 1 = 1%-25% mural thickness, 2 = 26%-50%, 3 = 51%-75%, or 4 = >75% allocated to each segment.

A positive result (≥2 adjacent segments [or 60° arc-equivalent if the defect crosses segmental boundaries] with ≥50% transmural extent of ischemia, scar, or ischemia-scar combination) will by protocol necessitate referral for invasive angiography ± FFR

#### Single-photon emission computed tomography

Single-photon emission computed tomography analysis will be both visual and quantitative. Local on-site reporting will include any regional wall motion abnormality (by visual analysis using the 17-segment model). Each segment scored as 0 = normal, 1 = mild hypokinesia, 2 = severe hypokinesia, 3 = akinesia, or 4 = dyskinesia.

Evidence of ischemia, by visual comparison of rest and stress scans, will be scored as 0 = normal, 1 = mild 51%-70%, 2 = moderate 31%-50%, 3 = severe 10%-30%, or 4 = absent <10% in each segment. Quantitative analysis will include summed rest score and summed stress scores, quantitative perfusion SPECT (QPS) defect extent (%), quantitative perfusion SPECT total perfusion deficit (%), end-systolic volume (mL), end-diastolic volume (mL), stroke volume (mL), and ejection fraction (%).

The presence of artifacts including subdiaphragmatic activity affecting the inferior wall, significant patient movement, anterior attenuation, inferior attenuation, and left bundle-brunch block artifact will be recorded.

A positive result (summed stress score ≥ 4), unless believed by the reporting clinician to represent attenuation artifact, will by protocol necessitate referral for invasive angiography ± FFR.

#### Cardiac CT

The total Agatson CAC score from the unenhanced scan will be determined. If the CAC score is >0 and <400, a contrast-enhanced scan will be performed.

Coronary stenosis will be graded as 0 = normal, 1 = minimal <25% stenosis, 2 = mild 25%-49%, 3 = moderate 50%-69%, 4 = severe 70%-99%, or 5 = occluded 100%. A positive result (either CAC >400 or any luminal stenosis ≥50% in an epicardial coronary artery ≥2.5-mm diameter) will by protocol necessitate invasive angiography ± FFR.

#### X-ray angiography and FFR

Invasive x-ray angiography will be interpreted visually by the performing clinician recording the coronary artery dominance, location, and visual degree (%) of all coronary stenoses in all major epicardial coronary arteries (with luminal diameter ≥2.5 mm). FFR measurement will be recorded in all arteries ≥2.5 mm with a visually recorded diameter stenosis ≥40% and ≤90%. Where FFR cannot be performed due to clinical/safety reasons, quantitative coronary angiography (QCA) will be performed using validated commercial vendor software. In this instance, QCA measurements will be made during offline analysis by a single independent blinded observer at the Glasgow Angiographic core laboratory. Lesions will be considered significant if a coronary artery segment (luminal diameter ≥2.5 mm) analyzed by QCA has a percentage diameter stenosis of ≥70% in one view or ≥50% in 2 orthogonal views.

### Protocol deviations

On occasion where the attending cardiologist overrules the protocol requirement to proceed to invasive coronary angiography, this will be recorded as a protocol violation.

### Annual follow-up

Annual follow-up over the subsequent 3 years will be undertaken to record death (including cause), other MACE, and withdrawal. For alive patients, medical history since randomization, including details and dates of acute coronary syndrome (ACS), emergency or elective revascularization procedure, any admission for cardiovascular cause will be obtained and verified from hospital or family practitioner records. Details of any recent cardiovascular investigations will be taken. In addition, Office for National Statistics monitoring will be sought for deceased patients to determine the certified causes of death.

### Primary end point

The primary end point is unnecessary invasive coronary angiography occurring within 12 months in each arm. This will be defined at the time of coronary angiography by an FFR measurement of >0.80 in all vessels ≥2.5 mm in a patient-based analysis (ie, at least 1 vessel with an FFR measurement of <0.8 will be required to define a patient with disease).

An “unnecessary angiogram” will be defined as one of the following:•A negative FFR and positive noninvasive test result (ie, a false-positive test result)•A negative FFR in a high PTL (61%-90%) patient that proceeds directly to invasive angiography in the NICE guidelines–based strategy arm (ie, a false-positive for the strategy)•A negative FFR and a negative noninvasive test result (ie, a true-negative strategy result in which the imaging result was “not believed” by the treating cardiologist—based on intention-to-treat principles)•A negative FFR and an inconclusive noninvasive test result in which angiography had to be performed to make the diagnosis (ie, failure of the strategy to produce a diagnosis)

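### The primary end point rests on FFR taken by an operator who will usually know the strategy, while core-laboratory assessment of the recordings is described only as quality assurance

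*Protocol article*

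**What the plan says.** All references are to the protocol article.

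- **Primary end point.** The timing and the instrument are fixed: "This will be defined at the time of coronary angiography by an FFR measurement", above 0.80 in every vessel of at least 2.5 mm, judged per patient ("at least 1 vessel with an FFR measurement of <0.8 will be required to define a patient with disease").
- **X-ray angiography and FFR.** The angiogram "will be interpreted visually by the performing clinician", and FFR is recorded in arteries with a visual stenosis of 40% to 90%. If FFR cannot be done for clinical or safety reasons, "QCA measurements will be made during offline analysis by a single independent blinded observer".
- **Invasive angiography and Fractional Flow Reserve.** "All sites will have FFR quality assurance core laboratory assessment of the FFR recordings". No further role is given to that assessment. Lesions visually below 40% receive a default FFR of 0.90; those above 90%, and occlusions, receive 0.50.
- **Investigation reporting.** As a general rule, "all clinical data from all noninvasive imaging modalities will be available for the reporting physician".
- **Referral rules.** A positive CMR, SPECT or CT leads to angiography by protocol. In the NICE arm, high-PTL patients go to angiography directly; low- and intermediate-PTL patients have CT or SPECT first.

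**The concern.** The end point is largely the false-positive rate of whatever sent the patient to angiography. The person who acquires and records the deciding FFR will normally know what that was, because the referral route reveals it. An operator who has just seen a positive scan may be readier to accept a value at or below the cut-off than one doing a direct angiogram with no prior imaging. Near 0.80 a small difference in reading turns an unnecessary angiogram into a necessary one. If that happens more in one arm than another, the treatment comparison is biased.

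The protection is uneven. The fallback measurement, QCA, has an independent blinded reader. The main measurement has a core laboratory that looks at recordings, but nothing says that its reading is masked or that it enters the end point.

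**Working it through.** **1. Inputs (Sample size; Study design).** 1,200 randomized 2:2:1 gives 480/480/240. After 20% noncompletion: 384/384/192. Projected rates: CMR 4.5%, SPECT 11.7%, NICE 30%. Two-sided 5%, continuity-corrected chi-square.

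**2. The plan's own power.** Power = Φ[(d − c − 1.96·SE0)/SE1], with d the difference in rates, c = ½(1/n1 + 1/n2), SE0 from the pooled rate and SE1 from the separate rates.

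- CMR vs SPECT: d = 0.072, c = 0.0026, SE0 = 0.01969, SE1 = 0.01952. Φ(1.578) = 94.3%; stated 94%.
- CMR vs NICE: d = 0.255, c = 0.0039, SE0 = 0.02973, SE1 = 0.03472. Φ(5.55) is above 99.9%; stated 99%.

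Both stated figures are reproduced. Changing who reads the FFR alters no input, so N and stated power stay as they are.

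**3. How many misreadings would matter.** Projected events: 384 × 0.045 ≈ 17 (CMR), 384 × 0.117 ≈ 45 (SPECT), 192 × 0.30 ≈ 58 (NICE). Take the projected counts as observed, and ask how many further CMR-arm events would have to have been read as FFR-positive for the true result to be nonsignificant. The comparator count is held fixed.

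- *CMR vs SPECT.* With 28 vs 45 the corrected P is 0.049. With 29 vs 45: 768 × (|29×339 − 355×45| − 384)² / (74 × 694 × 384 × 384) = 768 × 5760² / 7,572,750,336 = 3.36, P = 0.067. So 29 − 17 = 12 misread events, that is 12/29 = 41% of the true CMR-arm events.
- *CMR vs NICE.* With 86/384 vs 58/192: 576 × (|86×134 − 298×58| − 288)² / (144 × 432 × 384 × 192) = 3.76, P = 0.052. So 86 − 17 = 69 misread events, or 69/86 = 80% of the true CMR-arm events.

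**4. Illustration under assumed misreading shares.** The document gives no misreading rate, so these shares are assumptions. Suppose CMR and SPECT truly share an 11.7% rate (about 45 events per arm), and a share of true events is read as FFR-positive in the CMR arm only.

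| Assumed share | Patients moved | Rejection rate (corrected test) |
|---|---|---|
| 0% | 0 | 3.8% |
| 10% | 4.5 | 6.4% |
| 20% | 9.0 | 15.4% |
| 30% | 13.5 | 32.4% |

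This shows sensitivity to one-sided misreading. It does not show that such misreading occurs.

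**5. Which comparison the mechanism reaches.** Knowing a positive scan versus having no scan separates CMR patients from high-PTL NICE patients. It does not separate CMR from SPECT, where the operator has normally seen a scan in both arms. The mechanism therefore bears on the comparison with the wide margin (69 events). The comparison with the narrow margin (12 events) is reached only if operators trust a positive CMR more than a positive SPECT. The Background does tell readers that CMR was superior to SPECT in the earlier CE-MARC study, so this is possible, but the document offers no evidence of it.

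**The case against.** The case on the other side has real weight.

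- **FFR is an instrument-measured pressure ratio**, taken under a stated hyperaemia protocol with core-laboratory oversight at all sites. Discretion is limited. This stands, and it is why the point is an improvement rather than an error.
- **The article does not say that the core-laboratory value is excluded.** It fixes when and by what measurement the end point is defined, not whose reading prevails in a disagreement; a fuller protocol may settle that. This stands in part. The current wording still points to the value obtained at the procedure, and the only role named for the core laboratory is quality assurance.
- **Operator unblinding is inferred.** No sentence states it. The inference from the referral rules is strong, but it is an inference.
- **Re-reading a trace is only a partial cure.** It cannot re-create hyperaemia or wire position at acquisition. Patients given a default 0.90 or 0.50 from the operator's visual grade may have no trace to read. This stands in full.

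A reader might go further and estimate the bias by guessing how many patients have FFR measured and how many of those lie close to 0.80. The document gives neither figure. Only values just above the cut-off can move from unnecessary to necessary, and not all of them would. Any such percentage would be guesswork. A reader might also infer that the gap between seeing a scan and going straight to angiography threatens the 7.2-point CMR–SPECT difference (11.7% − 4.5%). It does not, because that contrast acts alike in those two arms.

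**Conclusion.** The concern holds as a design weakness that is cheap to reduce. The main measurement behind the primary end point is left to an operator who will usually know the strategy, while a core laboratory that could supply a masked reading is described only as quality assurance. The size of any resulting bias cannot be derived from the document.

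CMR versus NICE is robust at the projected rates. CMR versus SPECT is more fragile: 12 CMR-arm misreadings would separate a true nonsignificant result from the projected significant one. That would mean misreading 41% of the true events in one arm only, and it needs differential trust in the two tests. These margins assume the projected rates, 384/384/192 evaluable patients and no misreading in the comparator arm.

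**What to change.** State that the core-laboratory FFR value, read masked to arm and to the noninvasive result, defines the primary end point wherever a readable recording exists. Use the site value where it does not, and report a site-value analysis as a sensitivity analysis. At minimum, keep the site value as primary and prespecify the masked core-laboratory analysis as a sensitivity analysis. Clinical decisions stay with the site value.

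The cost is masking the recordings, a short rule on which value prevails, and some extra reading time if only a sample is now assessed. N stays at 1,200.

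The limits should be stated alongside. The change does not reach hyperaemia or wire position at acquisition, or the default values assigned from the operator's visual stenosis grade; the latter would need a blinded reading of the angiograms as well.

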#### Primary end point analysis

The difference in proportions of patients randomized to each arm with a study-defined unnecessary angiogram and 95%CI for this difference will be presented for summary purposes. A binary logistic regression will model the relative odds of receiving an unnecessary angiogram for CMR-guided care vs the group of interest (either NICE or SPECT-guided care pathways) when controlling for the minimization factors. The estimated odds ratios, 95% CI, and *P* values will be presented. An unadjusted analysis will compare the difference in the proportions between the 2 groups using a χ^2^ test.

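### The primary end point is defined twice, and the two definitions disagree on a negative angiogram in a patient who had no noninvasive test

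*Protocol article*

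**What the plan says.** The Primary end point section of the protocol article opens with a general definition. The end point is "unnecessary invasive coronary angiography occurring within 12 months in each arm", and it is "defined at the time of coronary angiography by an FFR measurement of >0.80 in all vessels ≥2.5 mm in a patient-based analysis". Nothing here depends on an earlier test. The abstract (Trial Design) agrees: "unnecessary angiography as defined by a normal (>0.8) invasive fractional flow reserve".

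The section then states that an unnecessary angiogram "will be defined as one of the following" and lists four cases:

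1. negative FFR after a positive noninvasive test;
2. "A negative FFR in a high PTL (61%-90%) patient that proceeds directly to invasive angiography in the NICE guidelines–based strategy arm";
3. negative FFR after a negative noninvasive test that the cardiologist did not believe, which is counted expressly on intention-to-treat grounds;
4. "A negative FFR and an inconclusive noninvasive test result in which angiography had to be performed to make the diagnosis".

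There is no residual category. The Analysis plan section puts all analyses on an intention-to-treat basis. The Primary end point analysis section compares "The difference in proportions of patients randomized to each arm with a study-defined unnecessary angiogram", so the denominator is everyone randomized and the numerator is whatever the definition admits.

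**The concern.** Cases 1, 3 and 4 each need a noninvasive result. Case 2 does not, but it is confined to high-PTL patients in the NICE arm. A patient randomized to CMR or SPECT who never has any noninvasive test, for example through non-attendance or because the clinician goes straight to angiography, and whose FFR is then negative, fits none of the four. Nor does a NICE patient with a PTL of 10% to 60% who bypasses CT or SPECT.

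Under the list these patients stay in the denominator as non-events. Under the opening definition they are events. The choice affects the primary outcome, and unless it is settled in advance it could be made after the data are known. For high-PTL patients the list also scores direct angiography with a negative FFR as an event in NICE and as a non-event in the imaging arms. That can lower the CMR rate relative to NICE for a reason unrelated to the performance of CMR.

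**Working it through.** **Step 1. The two definitions side by side, for a patient with negative FFR within 12 months and no noninvasive test**

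| Patient | Opening definition and abstract | List of four |
|---|---|---|
| CMR or SPECT arm, any PTL | event | not listed |
| NICE arm, PTL 10%-60%, CT or SPECT bypassed | event | not listed |
| NICE arm, PTL 61%-90% | event | event (case 2) |

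The definitions differ in the first two rows.

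**Step 2. The plan's own figures (Sample size section)**

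Inputs: N = 1,200, 20% noncompletion, allocation 2:2:1, two-sided 5%, continuity-corrected chi-square; projected rates 4.5% (CMR), 11.7% (SPECT) and 30% (NICE). Evaluable: 1,200 × 0.8 = 960, split 384:384:192. Solving the continuity-corrected two-proportion sample-size formula for power gives:

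- CMR versus SPECT, 384 per arm: 94.3% (stated 94%);
- CMR versus NICE, 384 versus 192: above 99.9% (stated 99%).

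The stated power reproduces. The gap in the list is not an error in that calculation.

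**Step 3. Possible size of the gap**

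The article gives no rate of bypassed tests, so the first two inputs are assumptions: 2% to 6% of an imaging arm have no noninvasive test, and 20% to 50% of those go to angiography. The third, 60% negative, borrows the Sample size section's figure of nearly 60% for high-PTL angiograms and applies it to all PTL groups.

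Missed share of the arm = untested × sent to angiography × negative:

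- low: 0.02 × 0.20 × 0.60 = 0.24 percentage points;
- high: 0.06 × 0.50 × 0.60 = 1.8 percentage points.

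The 4.5% is a weighted false-positive rate, so it describes tested patients and leaves out these events. The relative understatement therefore takes the full rate as its base:

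- low: 0.24 / (4.5 + 0.24) = 5%;
- high: 1.8 / (4.5 + 1.8) = 29%.

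**Step 4. Effect on the two comparisons**

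*CMR versus NICE.* The projected difference is 30 − 4.5 = 25.5 points. With 1.8 points added to CMR it is 23.7 points, and power stays above 99.9%.

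*CMR versus SPECT.* The projected difference is 11.7 − 4.5 = 7.2 points. Power when the missed events are counted:

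| Missed events | Both arms equally | CMR only |
|---|---|---|
| 0.24 points | 93.7% (difference 7.2) | 92.4% (difference 6.96) |
| 1.8 points | 89.8% (difference 7.2) | 70.2% (difference 5.4) |

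If both arms bypass equally, the absolute difference does not move and only the base rate rises. The CMR-only column is an extreme case that nothing in the article points to.

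**The case against.** A reader might infer that the plan has settled that a CMR or SPECT patient without the allocated test scores as a success. The article does not support that. The opening definition and the abstract would count this patient, and nothing says that the list overrides them. The list can be read as the expected routes to an event, and case 3 uses intention-to-treat precisely to count angiography outside the pathway. This objection stands: the defect is an unresolved contradiction.

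The scope is also narrower than the phrase *without the allocated test* suggests. The list speaks of a noninvasive result, not the allocated one, so a patient who had a different noninvasive test is covered. A scan begun and abandoned may count as inconclusive, which the article explains as the strategy failing to give a diagnosis. Table I also excludes several groups who could not be scanned, including those with a contraindication to CMR. What remains is the patient with no noninvasive test at all.

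Nor is the asymmetry complete. Direct angiography is the allocated strategy for high-PTL NICE patients, whereas in an imaging arm it departs from allocation. Departures are also missed in the rest of the NICE arm, and the list treats CMR and SPECT identically.

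Finally, a condensed article may leave classification details to the SAP. That would answer a complaint about missing detail. It does not answer two stated definitions of the primary end point that give different results for the same patient.

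**Conclusion.** The point holds as a contradiction within the primary end point definition. It is worth fixing but does not by itself undermine the trial. Applied literally, the list scores negative angiograms in wholly untested patients as non-events, except in the high-PTL NICE group. That departs from the stated intention-to-treat basis and can favour CMR over NICE.

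The size is not known. Under the assumptions above it is 0.24 to 1.8 percentage points of an arm, or about 5% to 29% of the CMR rate once these events are counted. Setting 1.8 against the list-based 4.5% would suggest 40%, but that base omits the missed events.

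The CMR versus NICE estimate could be somewhat inflated, but its conclusion would not change under the projected rates. A reader might also infer a bias towards CMR over SPECT. That requires the two arms to differ in how often the test is bypassed, and the article gives no evidence on this.

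**What to change.** State that any invasive coronary angiogram within 12 months of randomization counts as unnecessary in every arm if it shows no FFR-positive vessel of at least 2.5 mm (or, where FFR could not be done, no QCA-significant vessel), whether or not a noninvasive test was done. Keep the four cases as a descriptive classification of these events and add a fifth: no noninvasive test performed. Settle this before outcome data are examined by arm.

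The cost is one sentence in the definition and one more category to record. Whether the case report form already captures it cannot be seen from the article. The downside is that the imaging-arm rates become slightly less favourable.
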